## Blinding

N/A

## Code breaking

There is no blinding and a list for breaking the randomization code is not needed.

## Concomitant medications

Medications that are considered necessary for the safety and well-being of the subject can be given at the discretion of the investigator, unless otherwise specified as an exclusion criterion. Concomitant medications are reported in the CRF.

If treatment fails (positive culture for *Candida albicans* and symptoms), rescue medication of vaginal Clotrimazole 200 mg twice per week will be provided in both study groups for the rest of the study period. The regime of Clomitrazole is another established treatment for vulvovaginal *Candida albicans* infection.

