Our research group has previously done an *in vitro* study in which we analyzed the effect of FLZ and the antiseptic substance chlorhexidine gluconate’s (CHG) ability to kill fungal cells and to break down existing biofilm or prevent new biofilm formation [9]. The biofilm formation is an important stage for the fungal cells to attach to surfaces such as skin and mucosa and is considered a first step in the development of an infection [10]. In the biofilm, the fungus can hide from the immune system and also to some extent for various treatments aimed against the fungus. The results of the study showed that CHG was better than FLZ both at killing the fungal cells and preventing new biofilm from forming and dissolving already established "old" biofilm. This effect is absolutely crucial for successful treatment with antimycotics. These encouraging results form the basis of the planned study.

Hibitane® is an over-the-counter vaginal cream consisting of 1% chlorhexidine gluconate with the indication antiseptic use in vaginal examinations, especially during childbirth. The product has been used for a long time in various gynecological and obstetric surgical procedures. Hibitane® is approved during pregnancy and the cream is usually well tolerated [11]. There are only few studies that investigated how vaginal normal flora is affected by CHG. One human study showed a decrease in the number of lactobacilli a week after the vaginal application of 0.5% CHG every night for a week. After 30 days, the vaginal normal flora was basically fully recovered and the side effects were few [12]. In an animal study, no major effect was seen on the vaginal flora after 2 vaginal applications of CGH 0.25% at 24 hours apart [13].

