## Primary endpoint (variable)

The proportion of women in each group that has negative vaginal cultures for *Candida albicans* 1 week after active treatment.

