## Exclusion criteria

Subjects must not be included in the study if any of the following criteria are met:

- Severe somatic or mental illness (including liver and kidney failure and cardiac disease)
- Immunosuppressive medication
- Pregnancy
- Lactation
- Other ongoing gynecological infections
- Allergy to fluconazole or chlorhexidine gluconate
- Citalopram or other medication that might have impact on the QT interval (terfenadin, cisaprid, astemizol, pimozid, kinidin, erythromycin, halofantrin, amiodaron)
- Participation or recent participation (30 days) in a clinical study with an investigational product. Previous participation in this study.

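### A non-study antifungal before the primary culture is neither barred, scheduled to be asked about, nor classified, so a negative culture after it can count as clearance by the allocated drug

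*Protocol*

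**What the plan says.** Under the Concomitant medications section of the protocol, medications considered necessary for a woman's safety and well-being "can be given at the discretion of the investigator, unless otherwise specified as an exclusion criterion". The Exclusion criteria restrict immunosuppressive drugs and "Citalopram or other medication that might have impact on the QT interval". They name no antifungal, and the protocol has no separate list of prohibited medications.

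The same section says that "Concomitant medications are reported in the CRF". Table 1, however, ticks the item for health questionnaire and concomitant medications at Visit 2 only. The description of Visit 3 covers adverse events, culture and examination.

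The section also names a rescue antifungal for treatment failure, defined as a positive culture together with symptoms. It "will be provided in both study groups for the rest of the study period". Procedures and flow chart gives another rule for positive self-sampled cultures: the same study medication if it worked without adverse events, otherwise an individual option. That text places the prophylactic phase at Visits 2-3, although the visit list puts completion of prophylaxis at Visit 4.

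The primary endpoint is "The proportion of women in each group that has negative vaginal cultures for" C. albicans one week after active treatment. No condition concerns other antifungals. Intention-to-treat covers all randomised women. Per-protocol, as defined in the list of abbreviations, keeps women who completed the study with no protocol deviation.

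**The concern.** The trial is open, and women enter with acute symptoms. If a woman is not improving, she or the investigator may add an antifungal before the primary culture. If that drug clears the infection, the culture is negative and the endpoint as defined records a success for the allocated treatment. The protocol relies on the objectivity of the culture for its claim of low risk of bias, but an objective assay gives no protection against an added drug that itself turns the culture negative.

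If chlorhexidine is the weaker treatment, more women in that arm will be failing, so the added drug will mostly be used there. The observed difference then shrinks towards non-inferiority. A per-protocol analysis is the usual check on this, but it removes only deviations, and use approved under the concomitant-medication rule is not clearly one.

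**Working it through.** **Reproducing the plan's own figure.** Inputs from Sample size calculations: 86% clearance in both arms, limit 30 percentage points, alpha 5% (sidedness not stated), power 90%.

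n per arm = (1.645 + 1.282)² × 2 × 0.86 × 0.14 / 0.30² = 22.9, so 23 per arm and 46 in total, as stated. With a one-sided 2.5% test the result is 28.1, so 29 per arm and 58 in total. The stated size therefore rests on a one-sided 5% test. The statistical methods speak of 95% intervals, so both levels are shown below.

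**What follows from the text for a woman given an antifungal before Visit 3.**

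- Barred? No. The only limit is the exclusion criteria, and no antifungal is among them.
- A deviation? Not clearly, if the investigator judged it necessary. Not stated, if she took it on her own.
- Asked about? Not on a schedule. The item is ticked at Visit 2 only. The weekly diary starts in week 2 and collects compliance, symptoms and adverse events.
- Effect on the endpoint? A negative culture is a success, with no exception stated.

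**Illustration of size.** Assumptions: true chlorhexidine clearance lies exactly at the limit (56% v 86%); a share s of non-clearers takes another antifungal before the culture; that drug clears 86% of them (the protocol's fluconazole rate); 30 women per arm.

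- Observed chlorhexidine rate: pT = 0.56 + 0.44 × s × 0.86.
- Observed fluconazole rate: pC = 0.86 if only chlorhexidine women use it, or pC = 0.86 + 0.14 × s × 0.86 if the same share applies in both arms.
- Probability of declaring non-inferiority = Φ[(pT − pC + 0.30)/SE − z], where SE² = pT(1 − pT)/30 + pC(1 − pC)/30 and z = 1.645 or 1.96.

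Example, s = 10%, chlorhexidine only: pT = 0.598; SE = 0.1097; (0.598 − 0.860 + 0.300)/0.1097 = 0.345; Φ(0.345 − 1.645) = 9.7%.

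| s | pT | pC (both arms) | Chlorhexidine only, one-sided 5% / 2.5% | Both arms, one-sided 5% / 2.5% |
|---|---|---|---|---|
| 0 | 0.560 | 0.860 | 5.0% / 2.5% | 5.0% / 2.5% |
| 5% | 0.579 | 0.866 | 7.0% / 3.7% | 6.3% / 3.3% |
| 10% | 0.598 | 0.872 | 9.7% / 5.3% | 8.0% / 4.3% |
| 20% | 0.636 | 0.884 | 17.2% / 10.4% | 12.4% / 7.1% |

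An exact binomial calculation with the same unpooled test gives 7.0%, 9.7% and 17.2% for the chlorhexidine-only case at one-sided 5%.

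In women, 44% of 30 is about 13 non-clearers in the chlorhexidine arm. Shares of 5-20% are therefore roughly 0.7 to 2.6 women.

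**The case against.** The strongest reply is that the section has its own antifungal rule. Rescue requires a positive culture plus symptoms, and Visit 3 is the first scheduled culture after baseline, so planned rescue would normally follow the primary culture. On that reading, an antifungal given on symptoms alone departs from the specific rule, is a deviation, and leaves the per-protocol set. This is a reasonable reading, but the protocol does not state it. Procedures and flow chart also offers self-sampled cultures and an individual option in a phase printed as Visits 2-3, which lies before the primary culture.

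A second reply is that classification belongs in the SAP, which is attached but not shown. That is right for classification. But a SAP cannot classify use that no visit after baseline is scheduled to ask about. The general statement that concomitant medications go into the CRF helps only in part.

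Third, the size is assumed. The protocol gives no frequency for such use, and the rule applies to both arms. Applying the same share to fluconazole women lowers the inflation but leaves it above nominal.

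A reader might infer more than the text supports:

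- That any drug outside the exclusion criteria is allowed. It is not: the drug must be judged necessary for safety and well-being, at the investigator's discretion.
- That self-medication is permitted. The permission does not cover it, and the protocol is silent on its status.
- That fluconazole women may use the study cream and so contaminate the lactobacilli and biopsy comparisons, because "Hibitane® is an over-the-counter vaginal cream consisting of 1% chlorhexidine gluconate". Availability in a pharmacy is not permission under the protocol, and nothing in the document supports that contamination.

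**Conclusion.** The gap is real but narrower than a rule that openly allows antifungals. The protocol does not bar a non-study antifungal between randomisation and the Visit 3 culture, does not schedule a question about it, and does not say how a woman who used one is classified. Read as written, investigator-approved use can leave her in both analysis sets with a negative culture credited to the allocated drug.

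The likely direction is towards non-inferiority, provided use concentrates among women who are not improving. At one-sided 5% the illustration gives a false non-inferiority rate of about 7-17% (chlorhexidine arm only) or 6-12% (same share in both arms), against a nominal 5%. It rests on an assumed share of 5-20% of non-clearers, an 86% effect of the added drug, and true chlorhexidine clearance exactly at the limit. It shows that one to three women could matter in a trial of this size. It is not a forecast.

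**What to change.** - Add a CRF question at Visit 3 on any non-study antifungal taken since randomisation, with dates, whether prescribed or self-obtained.
- In the primary analysis, count a woman in either arm who used one before the Visit 3 culture as not cleared.
- List such use as a deviation for the per-protocol set.
- Report the as-cultured result as a sensitivity analysis.
- Reconcile the rescue rule in Concomitant medications with the relapse rule in Procedures and flow chart, including the phase printed as Visits 2-3. No view is taken on which treatment a woman should receive.

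The cost is one CRF item and a few lines of protocol and SAP text. The downside is that a few women with negative cultures count as failures, including some whom the allocated drug would have cleared. In the fluconazole arm this lowers the control rate, which is why the as-cultured result should stand beside the primary one.

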## Primary objective

To analyze if daily vaginal application of 8 ml of Hibitane® for one week and thereafter once a week for another 11 consecutive weeks is at least as effective as fluconazole 150 mg capsules every third day for the first three doses and thereafter 150 mg once a week for another 11 consecutive weeks regarding treatment- and prophylactic efficacy for recurrent vulvovaginal *Candida albicans* infection*.*

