## Secondary endpoint (variables)

1. The proportion of women in each group that has negative vaginal cultures for *Candida albicans* at 3 months’ follow-up after prophylactic treatment and at 6 months’ follow-up after the observational phase of the study.
2. Analysis of proportion of women with adverse events (AE) across treatment arms. The AEs will also be reported in descriptive terms and summarized for each treatment arm.
3. Proportion of women with symptom score > 2. Each symptom of typical discharge, itching, dryness of the skin/mucosa, burning and pain will generate 1 point of a composite index (range 0-5).
4. Proportion of women with examination score >2. Each finding of redness skin/mucosa, typical discharge, dry skin/mucosa, fissures skin/mucosa, visible candida hyphae in the microscope will generate 1 point of a composite index (range 0-5).
5. Proportion of women with reduced vaginal lactobacilli content in vaginal smears measured by a semi-quantitative method as normal or reduced quantity.
6. Proportion of women with relapse of *Candida albicans* infection between end of treatment and end of prophylactic treatment (1week post treatment to 3 months’ follow-up) and between 3- and 6 months’ follow-up after end of prophylactic treatment.
7. Proportion of women with possible toxic effect on the vaginal epithelium, defined as disruption and/or inflammation of the epithelial lining, analyzed from vaginal biopsies before and after treatment and prophylaxis.
8. Further analysis of mucosa inflammatory mechanism (histopathology and immunohistochemistry) and biofilm formation during and after treatment and prophylaxis, analyzed from vaginal biopsies. The methods for these *in vitro* exploratory analyses are not yet decided on.

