### Secondary endpoints (variables)

1. The secondary endpoint of treatment efficacy is the proportion of women in each group that has negative vaginal cultures for *Candida* albicans at 3 months’ and 6 months’ follow-ups, after end of prophylactic treatment. The cultures will be analyzed as described under 8.1.1.
2. Adverse events will continuously be registered during the study. The participants can fill out any AE in a web based digital weekly diary but also contact the research midwife when needed. AEs will be described and summarized and compared between treatment arms regarding proportion of women with AE.
3. A symptom and examination score (composite index 0-5) will be measured first at baseline/inclusion and then at 3 follow-ups; 1 week after treatment, 3 months’ follow-up after prophylactic treatment and at 6 months’ follow-up. The investigator will ask the participant for common symptoms of RVVC (typical discharge, itching, dryness of the skin/mucosa, burning and pain). Each present symptom will generate 1 point of the composite index (range 0-5). During the gynecological examination performed at inclusion and at each follow-up, typical clinical findings (redness skin/mucosa, typical discharge, dry skin/mucosa, fissures skin/mucosa, visible candida hyfae under the microscope) will be registered in the CRF. Each finding will generate 1 point of the composite index (range 0-5). The proportion of women in each treatment arm with symptom- and examination score >2 for both the will be used for statistical analyses.

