4. The content of lactobacillus in vaginal wet mount will be analyzed and semi-quantified first at baseline/inclusion and then at 3 follow-ups; 1 week after treatment, 3 months’ follow-up after prophylactic treatment and at 6 months’ follow-up. Routine procedure for wet mount (vaginal secretion with NaCl) will be performed and the amount of lactobacilli will be graded in a light microscope with high magnification (40x and 100x) (Olympus CX41) as either normal quantity (more lactobacilli compared to number of epithelial cell/view field) or reduced (less or absent lactobacilli compared to number of epithelial cell/view field). Differences in proportion of women with normal/reduced quantity between study groups x time will be analyzed. The two investigators will before the study starts, analyzed a number of wet mounts together for inter-rater reliability. All wet mounts will be photo documented via a camera connected to the microscope placed at the department of obstetrics and gynecology, Danderyd Hospital. These photos will be blinded and evaluated by the two investigators together.
5. Data on events of relapses will be collected during the prophylactic and observational phases of the study. The participants will be provided with equipment to collect self-sampled vaginal cultures for *Candida albicans* at home in case of new symptoms of infection. They can also contact the research midwife who could help out with the cultures if needed. Data on relapses will be reported in the CRF.
6. Biopsies from the vaginal mucosa will be used to study possible toxic effect on the vaginal epithelial cells. The biopsies will be taken at baseline/inclusion and at the 3 months’ follow-up and analyzed by histopathology and immunohistochemistry. The biopsies are 3-4 mm, taken by biopsy forceps after local anesthetics. The purpose of the biopsies is to investigate how CHG affect the vaginal mucosa causing possible toxic reactions of the epithelium and impairment of the local immune response. The biopsies will be microscopically examined using ordinary histopathological staining as well as immunohistochemistry for inflammatory and immunological markers. Also PCR analyses for antimicrobial peptides, cytokines, kemokins, cationic intrinsically disordered antimicrobial peptides (CIDAMP) will be performed. Biopsies from participants allocated to FLZ will serve as controls.

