## Statistical analyses

### Statistical methods

***Objective:*** The aim of this study is to analyze whether vaginal chlorhexidine gluconate (CHG) is at least as effective and safe as oral fluconazole (FLZ) as treatment and prophylaxis for recurrent vulvovaginal candidiasis.

***Study design:*** Randomized controlled non-inferior trial with 60 women randomly assigned to either vaginal chlorhexidine gluconate (N=30) or oral fluconazole (N=30). Baseline plus 3 follow-up visits (baseline/inclusion, 1 week, 3 months and 6 months) are planned.

***Primary outcome****:* Proportion of women with negative cultures for *Candida albicans* 1week post-treatment.

***Secondary outcomes****:*

- Negative cultures for *Candida albicans* at 3 months’ and 6 months’ follow-ups, after end of prophylactic treatment.
- Analysis of proportion of women with adverse events (AE). The AEs will also be reported in descriptive terms and summarized for each treatment arm.
- Proportion of women with symptom score > 2. Each symptom of typical discharge, itching, dryness of the skin/mucosa, burning and pain will generate 1 point of a composite index (range 0-5).
- Proportion of women with examination score >2. Each finding of redness skin/mucosa, typical discharge, dry skin/mucosa, fissures skin/mucosa, visible candida hyphae in the microscope will generate 1 point of a composite index (range 0-5).
- Proportion of women with reduced vaginal lactobacilli content in vaginal smears measured by a semi-quantitative method as normal or reduced quantity.
- Proportion of women with relapse of *Candida albicans* infection between end of treatment and end of prophylactic treatment (1week post treatment to 3 months’ follow-up) and between 3- and 6 months’ follow-up after end of prophylactic treatment.
- Proportion of women with possible toxic effect on the vaginal epithelium, defined as disruption and/or inflammation of the epithelial lining, analyzed from vaginal biopsies before and after treatment and prophylaxis.
- Further analysis of mucosa inflammatory mechanism and biofilm formation during and after treatment and prophylaxis, analyzed from vaginal biopsies. The methods for these *in vitro* exploratory analyses are not yet decided on.

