***Statistical methods:***

Analysis for differences over time for treatment efficacy, AEs, symptom- and examination score, impact on vaginal lactobacilli and relapses will be analyzed for all randomized patients (i.e. intent-to-treat ITT). Additionally, we will also examine efficacy for the per-protocol (PP) population. Four time points will be used to study the efficacy (proportion of participants with negative cultures for *Candida albicans*) in each treatment arm (baseline, 1w post-treatment, follow-up 3 and 6 months). We will examine the difference in means, proportions and median values using 95% confidence intervals (CI). The CI interval will be computed using 1) for a proportion in one sample and 2) logistic or multinomial logistic regression analysis.

Differences in baseline characteristics between the CHG and FLZ groups will be analyzed with Chi2 for categorical data, Mann Whitney U test for ordinal data, or t-test for continuous data to examine potential selection bias at randomization. Differences in drop-out rates across treatment arms will also be analyzed using Mann Whitney U test.

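### The 3- and 6-month culture endpoints score clearance after clotrimazole rescue or re-treatment as success for the allocated arm, which tends to dilute a true difference in prophylactic efficacy; the relapse endpoint makes up for this only in part

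*Protocol*

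**What the plan says.** - **Objective.** The primary objective compares the two 12-week regimens "regarding treatment- and prophylactic efficacy for recurrent vulvovaginal" *Candida albicans* infection. The primary endpoint is culture 1 week after active treatment, so it does not address prophylaxis.
- **Later culture endpoints.** Section 8.1.2 reads "The secondary endpoint of treatment efficacy is the proportion of women in each group that has negative vaginal cultures for" *C. albicans*, at 3 and 6 months. The list of secondary endpoints places the 6-month culture at "follow-up after the observational phase of the study", and section 10.2.1 repeats the endpoint at the "follow-ups, after end of prophylactic treatment". None of the three places mentions rescue or repeat treatment.
- **Population.** Section 10.2.1 states that treatment efficacy, adverse events, scores, lactobacilli and "relapses will be analyzed for all randomized patients (i.e. intent-to-treat ITT"). A per-protocol analysis is additional.
- **Rescue.** Concomitant medications covers women who are symptomatic and culture-positive, and states: "rescue medication of vaginal Clotrimazole 200 mg twice per week will be provided in both study groups for the rest of the study period". That paragraph also describes clotrimazole as an established treatment for this infection.
- **Re-treatment.** Under Procedures and flow chart, a woman with a positive culture at relapse is offered her study drug again if it worked and was tolerated, and otherwise an individual option. Section 7.1 also provides for additional treatment at relapse.
- **Relapse endpoint.** This counts "infection between end of treatment and end of prophylactic treatment (1week post treatment to 3 months", and then from 3 to 6 months. Women self-sample "at home in case of new symptoms of infection". A negative culture at Visit 3 is not required.

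**The concern.** A woman who still has a positive culture and symptoms at week 1 goes on clotrimazole until the study ends, so she is on an active third drug at both later cultures. If it clears her, she counts as a 3- and 6-month success for the drug that failed. The arm with more failures gains more from this, so the observed difference tends to be smaller than the true one.

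The prophylactic half of the primary objective rests on these cultures and on the relapse endpoint. The relapse endpoint has a weakness of its own. If women who never cleared count as relapse-free, the arm with more week-1 failures has fewer women who can relapse. With a moderate deficit in both phases, both later measures would understate it, and both errors would favour CHG.

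**Working it through.** **The plan's own figure.** With 86% success in both arms, a 30-point margin, one-sided 5% and 90% power: n = (1.645 + 1.282)² × 2 × 0.86 × 0.14 / 0.30² = 22.9, so 23 per arm and 46 in total, as section 10.4 states. This concerns week-1 culture, which is read before any rescue, so it is untouched.

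**Inputs.** From the protocol: FLZ clearance 86% (section 10.4) and 30 women per arm. Assumed:
- c: share cleared at week 1
- r: share of cleared women who stay clear; k = c × r is true success on the allocated drug
- g: share of failures treated before the culture, 0.25 to 0.75 (rescue requires symptoms, so g is below 1)
- s: clearance on extra treatment, 0.50 to 0.86

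**Observed success, three routes.**
- Common (extra treatment works equally in both arms): k + (1 − k)gs. The true difference is multiplied by (1 − gs).
- Mixed (clotrimazole for the never-cleared, allocated drug for relapses): k + (1 − c)gs + c(1 − r)gr.
- Own rate (all extra treatment works at the arm's own r): k + (1 − k)gr.

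**Case A, deficit in prophylaxis only.** c = 0.86 in both arms; r = 0.50 CHG, 0.75 FLZ. k = 0.430 vs 0.645, true difference −21.5 points.

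**Case B, deficit in both phases.** c = 0.70 vs 0.86; r = 0.60 vs 0.75. k = 0.420 vs 0.645, true difference −22.5 points.

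Observed difference in points, s = 0.50 to s = 0.86 where s enters:

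| g | Route | Case A | Case B |
|---|---|---|---|
| 0.25 | Common | −18.8 to −16.9 | −19.7 to −17.7 |
| 0.25 | Mixed | −20.2 | −20.3 to −18.9 |
| 0.25 | Own rate | −21.0 | −20.5 |
| 0.50 | Common | −16.1 to −12.3 | −16.9 to −12.8 |
| 0.50 | Mixed | −18.8 | −18.2 to −15.3 |
| 0.50 | Own rate | −20.6 | −18.4 |
| 0.75 | Common | −13.4 to −7.6 | −14.1 to −8.0 |
| 0.75 | Mixed | −17.5 | −16.0 to −11.7 |
| 0.75 | Own rate | −20.1 | −16.4 |

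Example, Case B, common, g = 0.50, s = 0.86: CHG 0.420 + 0.580 × 0.43 = 0.669; FLZ 0.645 + 0.355 × 0.43 = 0.798; difference −12.8. In Case A the mixed route does not depend on s, because both arms have the same share never cleared.

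**Chance that a 95% CI excludes zero** (Newcombe interval, exact binomial enumeration, 30 per arm, no drop-out):
- Case A: 39% on the true difference. As scored at g = 0.50: 25% to 18% (common), 33% to 35% (mixed), 39% (own rate).
- Case B: 43% on the true difference. As scored at g = 0.50: 27% to 20%, 32% to 25%, 33%. At g = 0.25, mixed: 36% to 32%.

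**Relapse endpoint, never-cleared women counted as relapse-free: c(1 − r).**
- Case A: 0.86 × 0.50 = 43.0% vs 0.86 × 0.25 = 21.5%. The deficit shows (43%).
- Case B: 0.70 × 0.40 = 28.0% vs 21.5%, only 6.5 points (8%). Among cleared women it is 40% vs 25%. The week-1 primary (70% vs 86%) excludes zero in 31% and has a lower limit above −30 points in 28%.
- Case C (c = 0.56 vs 0.86; r = 0.75 in both arms): 14.0% vs 21.5%, which wrongly favours CHG. The week-1 primary shows this gap (75%).

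**Not cleared at Visit 3, or relapse: 1 − k.** In Cases B and C, 58.0% vs 35.5%, the full 22.5 points (43%).

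**The case against.** **Left to the SAP.** The SAP is an attachment that is not shown, and handling of rescue is often placed there. However, the protocol itself fixes both the endpoint and the rescue rule. An SAP rule scoring rescued women as failures would change an endpoint that the protocol defines in three places without that condition.

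**Treatment policy.** Culture regardless of rescue in all randomised women is a coherent comparison, and section 7.1 treats additional treatment at relapse as part of administration. This stands as a reason to keep that analysis. It does not measure the allocated drug's prophylactic effect, which the primary objective names, and no endpoint separates clearance by clotrimazole from clearance by the allocated drug.

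**Open-label sampling.** A rule that depends on rescue depends partly on who reports symptoms and self-samples, and CHG's known irritation could prompt more sampling. This stands as a cost. It is limited because both treatment routes require a positive culture, but more sampling also finds more positives.

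**Other endpoints cover much of it.** Women not cleared at week 1 are failures in the primary endpoint, and relapses after clearance are counted. This stands for Cases A and C. In Case B the relapse shortfall depends on counting never-cleared women as relapse-free, which the protocol neither states nor excludes.

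**A stronger reading.** A reader might infer that the scoring sharply raises the risk of a false non-inferiority finding at 3 or 6 months. The documents do not support that. Section 10.4 sets the 30-point margin for the primary outcome only, and section 10.3 covers secondary outcomes with p-values adjusted for the false discovery rate.

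**Conclusion.** The point holds as a weakness in how the later culture endpoints are defined, and it should be fixed. As written, they credit the allocated arm with clearance achieved by rescue or re-treatment. With 25% to 75% of failures treated before the culture, a true deficit of about 22 points reads between about −21 and −8 points. The large losses need frequent extra treatment that works equally well in both arms. If it works only at each arm's own rate and the deficit arises only in prophylaxis, little is lost (−21.5 becomes −21.0 to −20.1).

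The relapse endpoint is a partial safeguard. It recovers a deficit arising in prophylaxis, but understates one in both phases if never-cleared women count as relapse-free (28.0% vs 21.5%, against 40% vs 25% among cleared women).

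A reader might also infer that a prophylactic failure of CHG would be hidden altogether, or that the main result is compromised. Neither follows: Case A shows in the relapse endpoint, a large week-1 gap shows in the primary, and the primary endpoint and sample size are unaffected. All inputs but the 86% are assumed, and with 30 per arm the chance of detection is low even with correct scoring.

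**What to change.** 1. For the 3- and 6-month culture endpoints, count women who received rescue or repeat antifungal treatment for a positive culture before that visit as not cleared. Report culture regardless of rescue alongside as supportive.
2. For relapse, analyse not cleared at Visit 3 or relapse in all randomised women. Report relapse among women culture-negative at Visit 3 descriptively.
3. Record start dates of rescue and re-treatment in the CRF. Concomitant medications are already reported there, but dates are not mentioned.

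**Cost.** Changing a secondary variable is a substantial change under section 13 and needs an approved amendment. Reported success will be lower in both arms, and a woman successfully re-treated with her own study drug will count as a failure. The endpoint will depend to some extent on symptom-triggered sampling in an open-label trial; the supportive culture analysis lets readers judge how far that matters.
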